**GPs/Nurses**							
Number of dementia diagnosis^1^		□	□	EMD^2^, self registration forms	□		□
Number of cognitive assessments^1^		□	□	EMD, self registration forms	□		□
Number of emergency consultations^1^	□		□	EMD, self registration forms	□		□
Adherence to guidelines	□		□	EMD, self registration forms/QIs	□		□
Change of knowledge	□		□	Own questionnaire			□
Change of Attitude	□		□	Own questionnaire			□
Change of skills	□		□	Own questionnaire			□
Age	□	□		Own questionnaire		□	□
Sex	□	□		Own questionnaire		□	□
Practice size	□	□		Own questionnaire		□	□
Practice experience	□	□		Own questionnaire		□	□
Percentage elderly in practice	□	□		Own questionnaire		□	□
Chronic care programs in practice	□	□		Own questionnaire		□	□

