### Bias control and randomisation

Randomisation will take place after measurement of baseline data. Duos of GPs and nurses will be randomly allocated to one of the two conditions: 1. Dementia Training Program (DTP) and 2. no training at all; control group. (Figure 1). Randomization will be concealed; a person who is not responsible for recruiting subjects and has no knowledge of the study conduct will perform it on a computer.

Cluster-randomisation will be performed in order to avoid contamination by the effects of possible exchange of information within a cluster. A cluster was defined as all GPs working in the same practice or as all GPs working together with the same nurse.

In order to assure an equal distribution of baseline characteristics, duos will be randomised with adaptive weights regarding cluster size (one vs. more than one GP), age, sex, high or low percentage of elderly patients in practice (< or > 15%), practice location (rural or urban area) and nurse affiliation (district or practice).

Adherence to guidelines will be assessed by two independent researchers. In order to exclude the possibility of detection bias, these researchers will be blinded to the outcome of randomization.

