### Outcome measures and data collection

Primary outcome measures are the numbers of cognitive assessments and dementia diagnoses over a period of nine months, which will be measured at baseline (T0) and nine months later, at the end of the study (T1). Secondary outcomes are GPs' and nurses' attitude, confidence and knowledge regarding dementia diagnosis and management, which will be measured at baseline (T0) and nine months later, at the end of the study (T1). Other secondary outcomes are the rate of adherence to national guidelines for dementia diagnosis and management, patient satisfaction, informal carer burden and satisfaction, number of emergency calls, visits and consultations. Baseline demographic characteristics collected from GPs and nurses are: age, sex, practice experience, practice size, percentage of elderly people > 65 years and the availability of chronic disease management programs in practice. Baseline demographic characteristics collected from patients and their informal caregivers are: age, sex and co-morbidity (Table 1).

**Table 1 T1:** Outcome measures

**Variable**	**Primary outcomes**	**Secondary outcomes**	**Background**	**Instrument/Source**	**T_0_**	**T_1_**	**T_x_**

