### Statistical analysis

In addition to a confirmatory analysis using the MANOVA-method, we will also perform an exploratory analysis. The aim of the exploratory analysis is to gain more insight into possible causal relations between the rate of success of the intervention components and the outcomes. Possible mediator variables are change in knowledge, attitudes and collaboration rate. We will design a path-model, specifying hypothesized relations between predictors, mediators, moderators, and effects, and we will test its goodness of fit with the data. In this way we hope to be able to specify the most plausible interdependence pattern between the variables used in the present study.

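### Table 1's change labels and a MANOVA with no named covariate point to an unadjusted change analysis of GP and nurse knowledge, attitude and skills; adjusting for the T0 score would be more precise at no cost

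*Protocol article*

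**What the plan says.** The GPs/Nurses block of Table 1 (protocol article, Outcome measures and data collection) lists three questionnaire outcomes as "Change of knowledge", "Change of Attitude" and "Change of skills". Only these row labels are used here, not the tick columns of the table.

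The running text of the same section words the domain differently: "Secondary outcomes are GPs' and nurses' attitude, confidence and knowledge regarding dementia diagnosis and management". It places the measurements at T0 and, nine months on, at T1. It does not use the word change.

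The Statistical analysis section gives one sentence on the confirmatory method: "In addition to a confirmatory analysis using the MANOVA-method, we will also perform an exploratory analysis". It names no covariates. Change appears again there, but only for the exploratory path model: "Possible mediator variables are change in knowledge, attitudes and collaboration rate".

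On timing, Bias control and randomisation states: "Randomisation will take place after measurement of baseline data". The adaptive-weight factors in that section are cluster size, age, sex, share of elderly patients, practice location and nurse affiliation. T0 questionnaire scores are not among them.

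**The concern.** If the change variables enter a MANOVA, or if T0 and T1 enter as repeated measures and the group-by-time term is tested, the quantity compared between arms is the raw difference in change. That contrast subtracts the whole T0 score, however weakly T0 predicts T1. Unless the two scores correlate perfectly, this subtracts too much. Precision is lost, and any chance difference between the arms at T0 is over-corrected.

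Better attitudes and knowledge are among the stated expectations for the programme, in both the abstract and the Objectives. With 2:1 allocation of 100 duos there are about 33 controls, so neither the loss of precision nor a chance imbalance at T0 can be dismissed as negligible.

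**Working it through.** **The plan's own figure first.** The article gives no sample-size figure for the knowledge, attitude or skills outcomes. Its one figure, for the primary outcome, is 91 GPs, and it reproduces:
- 50% versus 65%, two-sided 0.05, power 0.80, control to intervention 1:2, pooled variance: 126 + 252 = 378 patients.
- Design effect 1 + (5 − 1) × 0.05 = 1.20, so 378 × 1.20 = 453.6 patients.
- 453.6 / 5 = 90.7, rounded up to 91.

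The questionnaire outcomes do not enter this calculation, so nothing below alters it.

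**Inputs for the comparison.**
- From the article: 100 duos, two thirds to intervention, so about 67 and 33.
- Assumed: equal SD at T0 and T1; T0–T1 correlation r of 0.3 to 0.9 (the article gives none); one score per duo; no clustering.

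**Formulas, in units of the outcome SD.**
- Base factor: √(1/67 + 1/33) = 0.213.
- SE of the unadjusted change contrast: 0.213 × √(2(1 − r)).
- SE of the T0-adjusted contrast: 0.213 × √(1 − r²).
- Ratio of interval widths: √(2/(1 + r)), above 1 for every r below 1.

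| r | SE, change | SE, adjusted | Interval wider by |
|---|---|---|---|
| 0.3 | 0.252 | 0.203 | 24% |
| 0.5 | 0.213 | 0.184 | 15% |
| 0.7 | 0.165 | 0.152 | 8% |
| 0.9 | 0.095 | 0.093 | 3% |

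For an assumed true difference of 0.5 SD, power = Φ(0.5/SE − 1.96). Change versus adjusted gives 0.51 versus 0.69 (r = 0.3), 0.65 versus 0.78 (r = 0.5) and 0.86 versus 0.91 (r = 0.7). At r = 0.9 both are practically 1. Comparing T1 alone, with no use of T0, gives 0.65, so below r = 0.5 the raw change is less precise than ignoring T0 altogether.

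**Chance imbalance at T0.** Let d be the observed arm difference at T0 and τ the true effect. Given d, the expected T1 difference is τ + rd. Subtracting d leaves τ − (1 − r)d, so the change contrast is shifted by −(1 − r)d. The SD of d under randomisation is 0.213 SD. A difference of that size shifts the estimate by 0.5 × 0.213 = 0.11 SD at r = 0.5 and by 0.1 × 0.213 = 0.02 SD at r = 0.9, against the arm that started higher. Averaged over randomisations d is zero, so there is no bias overall.

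**Whether the label matters by itself.** If change is regressed on arm with T0 as covariate, T1 − T0 = a + τ·arm + b·T0. Moving T0 across gives T1 = a + τ·arm + (b + 1)·T0. The estimate of τ and its interval are the same. What costs precision is leaving T0 out of the model, not calling the outcome a change.

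**The case against.** The strongest reply is that the article never fixes this analysis. Three row labels are not an estimator, and no T1-minus-T0 formula is printed. The running text and the abstract name attitude, confidence and knowledge without calling them change. The table says skills where the text says confidence, which suggests loose shorthand. Covariates for secondary questionnaire outcomes are commonly left to a full protocol or analysis plan, which is not shown. The mediator sentence concerns the exploratory path model and says nothing about how arms are compared.

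Much of this stands. A reader might infer that the plan commits to a raw change score; the text does not go that far. A reader might also infer that the effect estimate would be biased; it would not, since the shift exists only given an observed imbalance. Nor would renaming the outcome as the T1 score be enough, as the algebra above shows. The magnitude depends on r, on equal SDs and, for power, on a 0.5 SD effect, none of which the article gives. The figures also ignore clustering, although GPs who share a practice or a nurse are randomised together.

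The reply does not remove the point. What the article does state, change as the outcome and MANOVA with no covariate as the method, leads most naturally to unadjusted change. That is a weaker choice than one the collected data already allow, and nothing in the article corrects it.

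**Conclusion.** The concern holds in limited form. The table labels and the named method together point to an unadjusted comparison of change, without stating it outright or ruling out adjustment for T0. Under that reading, intervals are about 3% to 24% wider than they need be for r between 0.9 and 0.3, and 15% wider at r = 0.5, assuming equal SDs and ignoring clustering. The loss vanishes as r approaches 1. Since the questionnaires are self-made and nine months and a training programme lie between the measurements, a correlation near 0.9 should not be taken for granted. The point is worth acting on, but it touches secondary outcomes only.

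**What to change.** State that, for knowledge, attitude and skills (or confidence), the arms are compared on the T1 score with the T0 score as a covariate, in separate models for GPs and nurses and with allowance for the randomised cluster. Analysing the change with T0 as covariate is equivalent. Unadjusted change may still be shown descriptively. If a full analysis plan already says this, a short clause in the Statistical analysis section and a matching label in Table 1 are enough.

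The cost is wording. Both scores are already to be collected, and T0 is measured before randomisation, so it is a valid covariate. The sample size and the primary analysis do not change.

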**Patients**							
Age	□	□		Own questionnaire		□	□
Sex	□	□		Own questionnaire		□	□
Co-morbidity	□	□		EMD		□	□
Satisfaction intervention	□		□	Own questionnaire	□	□	

**Informal carers**							
Age	□	□		Own questionnaire		□	□
Sex	□	□		Own questionnaire		□	□
Satisfaction intervention	□		□	Own questionnaire	□	□	
Burden informal caregiver	□		□	SSCQ^3^	□	□	

T_0 _is baseline measurement

T_1 _is follow up measurement, after 9 months

T_x _is 3 months after starting each assessment

^1 ^measurement of 'number' during a period of 9 months

^2 ^Electronic Medical Dossier

^3 ^Short Sense of Competence Questionnaire

Data on adherence to national guidelines, the number of emergency situations and the number of cognitive assessments and dementia diagnoses will be retrieved from GPs' Electronic Medical Records (EMD), from interviews with GPs and nurses and from self registration forms [41]. Self-made questionnaires will provide information on baseline characteristics, on data on GPs' and nurses' attitudes, competencies and knowledge regarding dementia diagnosis and management and on patient and informal carer satisfaction. Burden of informal carers will be assessed using the Short Sense of Competence Questionnaire (SSCQ) [42]. Data on duos' performance during the 'coaching phase' will be included in the analysis.

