## Methods

### Study design and setting

This study is an outcome assessor-blinded randomised controlled trial. A cluster-randomised design will be used to compare duos of GPs and nurses (Figure 1).

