## Discussion

In this paper we described the study design of a randomized controlled trial that evaluates the effects of a Dementia Training Program (DTP) for duos of GPs and primary care nurses. A novelty in this program is the training in fixed collaborative duos. We chose focus on collaboration, because dementia care management in collaborative interdisciplinary teams was found to be effective in improving the quality of care [31]. Another novelty in our approach is the inclusion of an individual coaching program in the DTP. This educational method appears to be highly effective modifying professional behaviour [32]. Whereas some studies used single interventions [27], we developed multifaceted intervention, since multifaceted interventions are usually more effective [33]. For the design and evaluation of the DTP, we used the MRC framework [44]. The exact content of the DTP will be described in more detail in a separate article. Methodologically strong elements in this study are the following. We avoid selection bias by computerized randomization and minimisation. Two independent blinded outcome assessors will contribute to overcoming detection bias. In addition to a confirmatory analysis, we will perform an exploratory analysis. In this way, we can clarify how certain intervention components influence the rate of success and through which pathways.

Below, we describe the design characteristics that may interfere with the reliability and validity of the future results. Firstly, the method of participant recruitment may threat the external validity of the study: GPs and nurses are free to decide whether they want to participate. This may mean that this group of participants is more interested in dementia care than their average colleagues. Therefore, they may be more motivated to learn and perform better than their non-participating colleagues would do after receiving the same training. In addition, they may already be taking better care of dementia patients and their caregivers than their non-participating colleagues. However, the possible effects of this bias would run counter to our hypotheses by negatively affecting the chances to detect differences between the experimental and the control group. These effects might affect the probability of making a type II error (incorrectly accepting H-0) but they cannot cause the making of a type I error (incorrectly rejecting H-0).

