Secondly, we cannot exclude the possibility of contamination arising by chance contacts and possible knowledge exchange between GPs and nurses from different allocation conditions. We try to overcome this problem by cluster randomization: GPs from the same practices and GPs working with the same nurses are allocated to the same group.

Finally, performance bias can occur. GPs and nurses are fully aware of their assignment to either the experimental or the control group. We try to overcome this problem by reminding participants in the control group every two months of their involvement in the study.

In spite of these elements of bias, the results of this trial may provide useful information for policy makers and developers of continuing medical education. The intervention is designed according to recently reported MRC guidelines and educational standards; exploratory analysis will reveal its successful elements. In the study design, bias is avoided if possible and still its setting is one of every day practice. Dissemination of the results of this study is planned for 2009.

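### Blinded assessment is described only for guideline adherence, while both primary counts rest on information supplied by unblinded GPs and nurses, so differential recording could bias the primary comparison

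*Protocol article*

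**What the plan says.** Methods, Study design and setting, makes the claim without qualification: "This study is an outcome assessor-blinded randomised controlled trial". The Discussion repeats it as a methodological strength: "Two independent blinded outcome assessors will contribute to overcoming detection bias".

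The task of these assessors is set out in Bias control and randomisation: "Adherence to guidelines will be assessed by two independent researchers", and "these researchers will be blinded to the outcome of randomization". Outcome measures and data collection places adherence among the secondary outcomes.

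The same section defines the primary endpoint: "Primary outcome measures are the numbers of cognitive assessments and dementia diagnoses over a period of nine months". The text after Table 1 takes these counts from the GPs' electronic records, "from interviews with GPs and nurses and from self registration forms". Table 1 also lists the record and the self-registration forms as sources for both counts. The same text adds that data on the duos' performance in the coaching phase will be part of the analysis.

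On the people who supply this information, the Discussion says: "GPs and nurses are fully aware of their assignment to either the experimental or the control group". The countermeasure it names, against performance bias, is "reminding participants in the control group every two months of their involvement in the study".

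**The concern.** A reader of the label and of the Discussion would take the primary outcomes to be protected by blinded assessment. The article shows that protection only for a secondary outcome. For the primary outcomes, the people who report the events are the people being trained, or not trained, to produce them.

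Contact about individual cases also differs by arm. Under Case-based coaching program, intervention nurses discuss their first two assessments with a coach around the time of the assessment. The first three patients of both nurses and GPs are reviewed at six weeks and three months, and coaches keep diaries. Controls have nothing equivalent. With clusters of 5 patients on average, three reviewed patients could be most of a duo's count. If this contact leads to more complete recording, or if coaching data add cases to the count, the intervention arm would show more assessments and diagnoses even if practice had not changed.

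The baseline measurement does not protect against this. Randomisation follows T0, so a recording difference that arises after allocation affects T1 only, and adjustment for T0 leaves it in place.

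**Working it through.** **Inputs** (Sample size calculations): 50% versus 65%, control to intervention 1:2, 5 patients per cluster, ICC 0.05, power 0.80, two-sided 0.05, 91 GPs.

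**1. The plan's own figure.** With k = 2, the pooled proportion is (0.50 + 2 × 0.65)/3 = 0.60.

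n(control) = [1.96 × √(0.60 × 0.40 × 1.5) + 0.8416 × √(0.50 × 0.50 + 0.65 × 0.35/2)]² / 0.15² = (1.176 + 0.508)² / 0.0225 ≈ 126.

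- Patients: 126 + 252 = 378.
- Design effect: 1 + (5 − 1) × 0.05 = 1.2, giving 453.6 patients.
- GPs: 453.6/5 = 90.7, so 91.

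The stated 91 is reproduced. The sample size is not at fault, and no new sample size follows from this point.

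**2. How much recording is at stake.** The planned effect per cluster is 5 × 0.65 − 5 × 0.50 = 3.25 − 2.50 = 0.75 patients over nine months. If nothing truly differs, the ratio of control capture to intervention capture that would imitate the whole effect is 0.50/0.65 = 0.77.

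**3. Spurious difference by capture rate.** The article gives no capture rates. *Assumptions:* no true effect, true share p in both arms, and full capture in the intervention arm. Control capture c is the proportion of true cases found by all sources together. The spurious difference is p × (1 − c).

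The rejection probability is that of the two-proportion test underlying the sample size, not of the planned MANOVA. It uses an effective size of 91 × 5/1.2 = 379.2, split into 126.4 and 252.8.

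| Control capture c | Difference, p = 65% | Rejection probability | Difference, p = 50% | Rejection probability |
|---|---|---|---|---|
| 95% | 3.3 points | 0.10 | 2.5 points | 0.07 |
| 90% | 6.5 points | 0.24 | 5.0 points | 0.15 |
| 85% | 9.8 points | 0.45 | 7.5 points | 0.28 |
| 77% | 15.0 points | 0.80 | 11.5 points | 0.56 |

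Worked row (c = 90%, p = 65%): the recorded shares are 0.585 and 0.65, a difference of 0.065. The standard error is 0.0526 under the null and 0.0531 under the alternative. Φ[(0.065 − 1.96 × 0.0526)/0.0531] = Φ(−0.72) ≈ 0.24. The opposite tail adds less than 0.001.

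**4. The blinding statements, by outcome.**

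| Outcome | Status | Source of information | Blinded assessment described? |
|---|---|---|---|
| Guideline adherence | Secondary | Records, interviews, forms | Yes, two researchers |
| Cognitive assessments | Primary | Records, interviews, forms | No |
| Dementia diagnoses | Primary | Records, interviews, forms | No |

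**The case against.** Clinicians cannot be masked in a trial of their own training, and the Discussion admits this openly. A condensed article may leave extraction and masking procedures to the full protocol, and this one does not say who extracts the primary counts. That is fair, and silence on procedure is not the point here. The point is that the article makes a trial-wide claim and then describes its basis for one secondary outcome only. Masking the extractor would also not mask the clinicians who supply the information.

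The controls are not left alone. They are contacted every two months and are offered the training after the trial, and both may support their recording. This stands as a mitigating factor, but the reminders are offered only against performance bias, and differential recording is not addressed.

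Using three sources is a defensible choice. If they are combined, a case is lost only when all of them miss it. This stands too: the capture rates above must be read as overall rates, and the 77% row is an extreme.

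Some stronger readings are tempting but not supported:

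- A reader might infer that self-registration cannot exist for the nine months before T0, so that T0 and T1 use different sources. The article does not say when forms are issued or whether they may be completed retrospectively, and the timing marks in Table 1 cannot be read reliably.
- A reader might take it as fact that coaching raises registration. The coaching is described as covering assessment, work-up and management, not form completion. Its effect on recording is plausible but is an inference.
- A reader might conclude that the record alone should be the primary source. Unblinded GPs write that record too. Under the programme the nurse carries out the assessment, and the nurse may be a district nurse. A record-only count could therefore miss nurse-performed assessments, possibly more often in the intervention arm.

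**Conclusion.** The concern holds in a limited form. The article states outcome-assessor blinding for the trial as a whole but describes it for guideline adherence only. Both primary counts depend on information from unblinded participants, and case-level contact differs by arm. Differential recording could therefore bias the primary comparison.

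The size is unknown. Under the stated assumptions with a true share of 65%, an overall control shortfall of 5 to 15% gives about 3 to 10 of the planned 15 points and raises the false-positive probability from 0.05 to between 0.10 and 0.45. With a true share of 50%, the same shortfalls give 2.5 to 7.5 points and 0.07 to 0.28. A reader might infer that recording alone would produce the whole planned effect. That would need controls to lose 23% of cases across all sources while the intervention arm loses none, and nothing in the article indicates a gap of that size. The Discussion also says only that the blinded assessors contribute to overcoming detection bias, so it should not be read as claiming that the bias is eliminated.

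**What to change.** 1. Apply one identical ascertainment rule, to the same sources, in both arms and in both nine-month periods.
2. Exclude coaching-derived data, including the coaches' diaries, from the primary counts. They remain available for the exploratory path model.
3. Have the two blinded researchers already planned classify allocation-masked case material for both primary outcomes as well as for adherence.
4. Prespecify a record-only count as a sensitivity analysis, not as the sole primary source, for the reasons given under the objection.
5. If step 3 is not feasible, restrict the outcome assessor-blinded label and the detection-bias statement to guideline adherence, and state that the primary counts are reported by unblinded participants.

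The cost is some masking and classification work for researchers already in the plan, plus changes of wording. Masked classification does not remove under-reporting by unblinded clinicians. The common rule and the record-only analysis limit that problem and make it easier to see, and the report should say that it remains.
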